Foot deformity	The Manchester Scale [57].	• The presence of hammer/claw toes, hallux abducto valgus, bony prominences (e.g. prominent metatarsal heads), Charcot neuroarthropathy and any other foot deformities (e.g. forefoot pad atrophy) will be assessed visually [57]	Foot deformity will be recorded with the presence of ≥1 foot deformity on either foot.
		• Hallux abducto valgus will be graded in accordance with the Manchester Scale (no deformity = 1, mild deformity = 2, moderate deformity = 3, severe deformity = 4) [57, 58]	
		• Foot deformity will be recorded as ‘present’ or ‘absent’	
Range of motion (1^st^ metatarsophalangeal joint)	Goniometer.	• Passive range of dorsiflexion at the 1^st^ metatarsophalangeal joint will be measured using goniometry with the ‘static non-weightbearing technique 1’ described by Hopson et al. [60]	Range of motion <65° indicates limited joint mobility of the first metatarsophalangeal joint [60].
Plantar pressures	Tekscan Matscan® system (Tekscan Inc, South Boston, MA, USA).	• Plantar pressures will be assessed during level barefoot walking with the Tekscan Matscan® system [64, 94]	Mean peak plantar pressures will be investigated to determine whether they are predictive of foot ulceration.
	5.7 mm thick floor mat (436 × 369 mm), 2288 resistive sensors (1.4 sensors/cm^2^), dynamic events captured with scan rates of 440 Hz.	• The two-step gait initiation protocol will be used, with the technique as described by Zammit et al. [64], except that both feet will be assessed	
	FootMat™ 7.0 software (Tekscan Inc, South Boston, MA, USA).	• The mat will be calibrated for each patient using that patient’s own weight before each testing session	
		• Peak plantar pressure will be measured at seven regions of the foot, including the heel, midfoot, first metatarsophalangeal joint, second metatarsophalangeal joint, 3–5 metatarsophalangeal joints, hallux and lesser toes [64]	
		• The mean peak plantar pressure values of the three trials of each foot will be used for final data analysis [64, 95]

**Table 5 Tab5:** Baseline data: footwear assessment

Footwear assessments	Procedure	Diagnosis/study definition

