Fit, general features, style and condition	• The fit (length, width, depth), general features (fixation, forefoot sole flexion point, heel height, materials), style and condition of footwear will be assessed based on the footwear assessment tool described by Barton et al. [65]	Footwear will be deemed inappropriate if there are any issues with shoe fit, inappropriate style or condition.

**Table 6 Tab6:** Baseline data: dermatological assessment

Dermatological assessments	Procedure	Diagnosis/study definition
Skin pathology	• The presence of hyperkeratosis (callus), heloma dura (corns), uraemic pruritus, xerosis, calciphylaxis and other skin pathologies will be assessed visually [18, 66, 67, 70–72]	Skin pathology will be recorded with the presence of ≥1 skin pathology on either foot.
	• Severity of xerosis will be graded in accordance with the Xerosis Severity Scale (mild = 1–2, moderate = 3–4, severe = 5–6) [66, 67]	
	• Skin pathology will be recorded as ‘present’ or ‘absent’	
Nail pathology	• The presence of half-and-half nail, absent lunula, onychomycosis, onychocryptosis (ingrown nail), onychauxis (thickened nail) and other nail pathologies will be assessed visually [70, 71]	Nail pathology will be recorded with the presence of ≥1 nail pathology on either foot.
	• Nail pathology will be recorded as ‘present’ or ‘absent’

**Table 7 Tab7:** Baseline data: history of lower extremity complications

Lower extremity complication	Procedure	Diagnosis/study definition
Foot ulceration	• Past or current foot ulcers will be determined by self-report, observation and medical record review	A foot ulcer will be defined as a ‘full thickness skin break that is distal to the ankle joint, and may extend into or through the dermis and involve deeper structures such as bones, tendons, joint capsules and ligaments’ [41, 55, 73].
	• The location, type and duration of a current foot ulcer will be recorded	
Lower extremity amputation	• Past lower extremity amputations will be determined by self-report, observation and medical record review	A lower extremity amputation will be defined as a ‘complete loss of any part of the lower extremity [74], including any digit, partial foot amputation or higher’.
	• Lower extremity amputations will be classified as minor (below ankle) or major (above ankle)	Lower extremity amputations resulting from trauma or the presence of a tumour will not be recorded.

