		A major amputation will be classified as a loss of limb above the ankle, or minor amputation if below the ankle [74, 75].

**Table 8 Tab8:** Baseline data: foot health care behaviours and podiatry attendance

Foot health care behaviours and podiatry attendance	Procedure	Diagnosis/study definition
Foot health care behaviours	• Foot health care behaviours will be investigated via participant interview	Foot health care behaviours will be considered ‘poor’ if the participant answers “no” to ≥3 questions.
	• Participants will be asked to respond “yes” or “no” to the following questions:	
	(i) Do you inspect your feet daily?	
	(ii) Do you avoid walking barefoot?	
	(iii) Are you able to reach your feet?	
	(iv) Do you treat your own nails and skin lesions?	
	(v) Have you ever seen a podiatrist before?	
Podiatry attendance	• Podiatry attendance will be investigated via participant interview	Podiatry attendance will be recorded as the number of visits per year.
	• Participants will be asked: How many times have you seen a podiatrist in the last 12 months?	

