#### Neurological assessment

The presence of peripheral neuropathy will be assessed using a Baily Instruments Ltd® (Salford Quays, UK) Semmes-Weinstein 5.07/10 g Monofilament and a Horwell® (Wilford, Nottingham, UK) Neurothesiometer, based on the recommendations of the American Diabetes Association [35]. These tests will evaluate loss of protective sensation and vibration perception threshold, respectively.

A recent systematic review reported that a failed Semmes-Weinstein monofilament test is a significant and independent predictor for subsequent foot ulceration in patients with diabetes [36]. A systematic review of validation studies found that testing of loss of protective sensation with a 10 g monofilament has reported sensitivity of 57 to 93 % and specificity of 75 to 100 % for detecting diabetic neuropathy [36]. The Baily Instruments Ltd® monofilament was selected for use in this study as it is one of the most accurate monofilaments to produce a 10 g buckling force (100 % buckling within ±1.0 g of 10 g) [37]. The plantar aspects of the hallux, first and fifth metatarsals will be assessed [38, 39].

The vibration perception threshold will be evaluated as it can identify those with less severe forms of neuropathy (i.e. before loss of protective sensation is evident clinically) [40]. A review of validation studies found that testing of vibration perception threshold with either a Neurothesiometer or Biothesiometer has reported sensitivity (77 to 100 %) and specificity (73 to 81 %) ranges for detecting diabetic neuropathy [40]. A vibration perception threshold of >25 V (tested on the apex of the hallux) in at least one foot will be used as the cut off value in this study, as it has been associated with a high cumulative risk of neuropathic ulceration [41, 42].

Peripheral neuropathy will be recorded if any of the following are present:Documentation of known peripheral neuropathy in the medical records;Monofilament score of <3/3 (either foot) [36];Vibration perception threshold >25 V (either foot) [40–43].

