#### Biomechanical assessment

Anomalies of foot structure have been found to be predictive of foot ulceration in prospective studies [41, 55, 56]. The grading of hallux valgus will be evaluated using the Manchester Scale [57], as it provides a valid representation of the degree of hallux valgus deformity [58]. Intra- and inter-rater reliability have been found to be excellent, with kappa (κ) values of 0.77 and 0.86, respectively [57]. Foot deformity will be recorded if any of the following are present:Hallux abducto valgus (graded in accordance with the Manchester Scale) [35, 57];Hammer/claw toes [35];Bony prominences (e.g. prominent metatarsal heads);Charcot neuroarthropathy [35];Other (e.g. forefoot pad atrophy).

Limited joint range of motion (e.g. first metatarsophalangeal joint) has also been associated with an increased risk of foot ulceration in prospective and case–control studies [55, 56, 59].

Dorsiflexion range of motion of the first metatarsophalangeal joint will be assessed in accordance with the ‘static non-weightbearing technique 1’ described by Hopson et al. [60]. This technique has been shown to be a reliable clinical measurement (ICC = 0.95). Limited range of motion at the first metatarsophalangeal joint will be documented if:Passive, non-weightbearing dorsiflexion is <65° (either foot) [60].

Elevated peak plantar pressures have been found to be a statistically significant predictor of diabetic foot ulceration in prospective studies [61–63]. Peak plantar pressures will be assessed during level barefoot walking using a two-step gait initiation protocol [64] with the Tekscan Matscan® system (Tekscan Inc, South Boston, MA, USA). Peak plantar pressures will be measured at seven regions of the foot, including the heel, midfoot, first metatarsophalangeal joint, second metatarsophalangeal joint, third to fifth metatarsophalangeal joints, hallux, and lesser toes [64]. The mean peak plantar pressure values of the three trials (of each foot) will be used for the purposes of analysis.

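### Several foot measures collected on continuous or graded scales enter the models only as either-foot binaries, and foot-care item (iv) is scored in an unexplained direction

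*Protocol article*

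**What the plan says.** All references are to the protocol article.

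- **Skin and nails (Table 6).** "Skin pathology will be recorded with the presence of ≥1 skin pathology on either foot", and likewise "Nail pathology will be recorded with the presence of ≥1 nail pathology on either foot". Each list has six categories, the last being 'other'. The same table says "Severity of xerosis will be graded in accordance with the Xerosis Severity Scale", but that grade is not in Table 9.
- **Deformity (Table 4).** "Foot deformity will be recorded with the presence of ≥1 foot deformity on either foot", from five categories including 'other'. "Hallux abducto valgus will be graded in accordance with the Manchester Scale", on a scale of 1 to 4; this grade is also absent from Table 9.
- **Joint range (Biomechanical assessment).** Dorsiflexion is measured in degrees and recorded as limited if below 65° on either foot.
- **Neuropathy (Neurological assessment).** "Peripheral neuropathy will be recorded if any of the following are present": a record diagnosis, a failed monofilament test, or a vibration threshold above 25 V in either foot.
- **Arterial disease (Arterial assessment).** Any of a record diagnosis or revascularisation history, two or more absent pulses, toe-brachial index ≤0.6 or ankle-brachial index ≤0.9. Calcification is a separate flag.
- **Model form (Table 9).** All of these stand in the categorical column. Peak plantar pressure, blood tests, body mass index and the durations of diabetes and dialysis stay continuous.
- **Foot-care score (Table 8).** Three or more 'no' answers out of five make behaviour 'poor'. Item (iv) asks "Do you treat your own nails and skin lesions"; item (v) asks whether the participant has ever seen a podiatrist. A 'no' to either counts towards 'poor'.

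**The concern.** The study exists to find predictors of ulceration, and it measures several candidates more finely than it plans to model them. Under the 'any' rule, mild xerosis and calciphylaxis receive the same code, as do a mild hallux valgus and a Charcot foot. If such a code is present in most participants, it varies little and can hardly predict anything. A null result for skin, nails or deformity might then reflect the coding rather than the biology. The article also justifies vibration testing by its ability to detect milder neuropathy; a 25 V cut merged with two other routes hides that gradation.

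The foot-care score raises a separate question. A participant whose nails and callus are treated by a podiatrist answers 'no' to item (iv) and moves towards 'poor', while item (v) credits the same contact. The article gives no reason for scoring item (iv) this way.

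**Working it through.** The article states no figure for information lost by coding, so there is none to reproduce. Its sample size of 430 comes without reference incidences or exposed shares and cannot be rebuilt. It is used here only for the number left after 20% loss: 430 × 0.80 = 344.

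**1. Loss from one cut.** Assume a normal predictor with a linear effect. The share of information kept when it is cut at prevalence p is φ(z_p)² / [p(1 − p)]. Power is Φ(2.80 × √share − 1.96), starting from 80% on the continuous scale.

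| Prevalence of 'present' | Share kept | Power |
|---|---|---|
| 50% | 0.64 | 61% |
| 70% | 0.58 | 57% |
| 80% | 0.49 | 50% |
| 90% | 0.34 | 37% |
| 95% | 0.22 | 26% |

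The formula is symmetric in p and 1 − p. The smallest possible loss is 1 − 0.64 = 36%. The loss passes 50% only above about 79% or below about 21% prevalence.

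**2. The 'any' composites.** With k independent components of equal prevalence q (assumed), the composite has prevalence P = 1 − (1 − q)^k. For k = 6:

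- q = 10%: 1 − 0.9⁶ = 47%
- q = 20%: 1 − 0.8⁶ = 74%
- q = 30%: 1 − 0.7⁶ = 88%

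The squared correlation of one component with the composite is q(1 − P) / [(1 − q)P]: 0.126, 0.089 and 0.057 respectively. If only one lesion type matters, the composite carries about 6-13% of its variance.

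**3. Smallest detectable hazard ratio for a binary.** At 80% power and two-sided 5%, this is exp(2.80 / √[E·p(1 − p)]) for E events. The article gives no expected event count, so E is an assumption. Two scenarios are 40-50 events, and about 72 events. The latter applies the only incidence quoted (210 per 1000 person-years, dialysis patients with diabetes) to all 344 for one year: 0.210 × 344 = 72.

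| Prevalence | E = 40-50 | E = 72 |
|---|---|---|
| 50% | 2.4-2.2 | 1.9 |
| 90% | 4.4-3.7 | 3.0 |
| 95% | 7.6-6.2 | not computed |

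**4. Foot-care score.** Reversing item (iv) changes the class only when exactly two of the other four answers are 'no'. That is C(4,2) = 6 patterns, times two answers to (iv): 12 of 32 patterns. This counts patterns, not participants.

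**The case against.** The strongest reply has five parts.

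- **The size depends on unknown prevalences.** This stands. A reader might infer that most of the information is discarded. The article does not support that: a median cut keeps 64%, and no prevalence is given.
- **The cut-offs are pre-specified and cited.** For 25 V the text adds an association with cumulative ulcer risk. This supports reporting the thresholds and avoids data-driven cut-points. It does not make them the only sensible modelled form.
- **The formula fits unions of different conditions poorly.** This stands. The 36% figure applies to range, volts and indices. For skin, nails and deformity, the relevant issue is prevalence and dilution, as in steps 2 and 3.
- **Functional form belongs in the analysis plan, and the raw values are still collected.** This is partly right: nothing is lost at data collection. But Table 9 does state the form, and following it as written incurs the loss.
- **Replacing every binary would do harm.** This stands. Volts alone would drop the monofilament and record diagnoses; toe-brachial index alone would drop pulses, revascularisation and ankle index; hallux valgus grade alone would drop Charcot foot and claw toes. Neuropathy yes/no is also one of the two predictors behind the sample size.

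On the score, items (i) to (iv) can be read together as self-care and the ability to do it, and item (v) asks about any past contact, not current treatment. One 'no' cannot by itself make behaviour 'poor'.

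**Conclusion.** The point holds in a limited form. Joint range, vibration threshold, the pressure indices and the skin, nail and deformity findings enter Table 9 only as either-foot binaries or inside them, and two collected grades are unused. Under a normal predictor with a linear effect, each cut costs at least about 36% of the information, and more than half only outside about 21-79% prevalence. For the 'any' composites the loss ranges from modest to severe, depending on prevalences and event counts that the article does not give.

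Two broader readings fail. It is not true that all foot measurements are collapsed, since peak plantar pressure stays continuous. Nor is the foot-care score shown to contradict itself throughout: the tension is between items (iv) and (v) only, and it is an unexplained scoring direction rather than a demonstrated error. Which direction is right is not judged here.

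**What to change.** In Table 9 and the analysis plan still to be agreed:

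1. Model first metatarsophalangeal range in degrees (worse foot) instead of the 65° binary. Model the number of distinct skin lesion types and of distinct nail lesion types instead of the two 'any' binaries. Keep the binaries for description.
2. Retain the neuropathy, arterial disease and deformity composites. Add pre-specified models with vibration threshold in volts (flagging participants tested at an alternative site), toe-brachial index (worse foot, with the calcification flag), hallux valgus grade and xerosis grade. State whether the parent composite stays in each of these models.
3. Reconcile the direction of item (iv) with item (v) and give the reason. Also analyse the score without item (iv), and report item (iv) separately.

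The cost is wording in Table 9 and the analysis plan, with no new data. Step 1 swaps one term for one; steps 2 and 3 add a few. Per-unit effects are less familiar than clinical cut-offs, and a lesion count gives every lesion type equal weight, which should be stated as a limitation.

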#### Neurological assessment

The presence of peripheral neuropathy will be assessed using a Baily Instruments Ltd® (Salford Quays, UK) Semmes-Weinstein 5.07/10 g Monofilament and a Horwell® (Wilford, Nottingham, UK) Neurothesiometer, based on the recommendations of the American Diabetes Association [35]. These tests will evaluate loss of protective sensation and vibration perception threshold, respectively.

A recent systematic review reported that a failed Semmes-Weinstein monofilament test is a significant and independent predictor for subsequent foot ulceration in patients with diabetes [36]. A systematic review of validation studies found that testing of loss of protective sensation with a 10 g monofilament has reported sensitivity of 57 to 93 % and specificity of 75 to 100 % for detecting diabetic neuropathy [36]. The Baily Instruments Ltd® monofilament was selected for use in this study as it is one of the most accurate monofilaments to produce a 10 g buckling force (100 % buckling within ±1.0 g of 10 g) [37]. The plantar aspects of the hallux, first and fifth metatarsals will be assessed [38, 39].

The vibration perception threshold will be evaluated as it can identify those with less severe forms of neuropathy (i.e. before loss of protective sensation is evident clinically) [40]. A review of validation studies found that testing of vibration perception threshold with either a Neurothesiometer or Biothesiometer has reported sensitivity (77 to 100 %) and specificity (73 to 81 %) ranges for detecting diabetic neuropathy [40]. A vibration perception threshold of >25 V (tested on the apex of the hallux) in at least one foot will be used as the cut off value in this study, as it has been associated with a high cumulative risk of neuropathic ulceration [41, 42].

Peripheral neuropathy will be recorded if any of the following are present:Documentation of known peripheral neuropathy in the medical records;Monofilament score of <3/3 (either foot) [36];Vibration perception threshold >25 V (either foot) [40–43].

#### Arterial assessment

The presence of peripheral arterial disease will be assessed by palpating pedal pulses (i.e. dorsalis pedis and posterior tibial) and by calculating the toe-brachial pressure index and the ankle-brachial pressure index bilaterally. Symptoms for peripheral arterial disease (i.e. intermittent claudication and rest pain) will not be assessed in this study, as it is likely that there is a high prevalence of *asymptomatic* peripheral arterial disease in this population, due to a high co-prevalence of diabetes, infections and neuropathy [44]. A combination of the toe-brachial pressure index and ankle-brachial pressure index measurements will allow for a more accurate representation of the prevalence of peripheral arterial disease, due to the known high prevalence rates of medial arterial calcification in dialysis patients [45, 46].

As per the recommendations of Leskinen et al. [45], toe-brachial pressure indices ≤0.6 and/or ankle-brachial pressure indices ≤0.9 will indicate the presence of peripheral arterial disease. The SysToe® (Atys Medical, Soucieu-en-Jarrest, France) system was chosen to determine the toe systolic pressure as it has been shown to be a valid and reliable clinical assessment tool (Intraclass Correlation Coefficients, ICC = 0.89 and 0.91 for the right and left sides respectively) [47–49]. The Doppler ultrasound technique will be used to assess the ankle and brachial systolic pressures, as it is known to be a valid and reliable assessment method in the detection of peripheral arterial disease [50, 51]. In addition, ankle-brachial pressure indices ≤0.9 have been reported to have a high sensitivity (75 %) and specificity (86 %) for the diagnosis of peripheral arterial disease in pooled meta-analyses [50].

Peripheral arterial disease will be recorded if any of the following are present:Documentation of known peripheral arterial disease in the medical records and/or history of lower extremity revascularisation procedure;Absence of ≥2 pedal pulses after palpating the dorsalis pedis and posterior tibial pulses on both feet [52];Toe-brachial pressure index ≤0.6 (either foot) [44, 45, 53] and/or ankle-brachial pressure index ≤0.9 (either foot/lower extremity) [44, 45, 50, 53, 54].

Arterial calcification will be recorded if any of the following are present:Ankle-brachial pressure index >1.3 (either foot/lower extremity) [44, 54];Non-compressible peripheral arteries (i.e. systolic pressure >240 mm Hg).

#### Biomechanical assessment

Anomalies of foot structure have been found to be predictive of foot ulceration in prospective studies [41, 55, 56]. The grading of hallux valgus will be evaluated using the Manchester Scale [57], as it provides a valid representation of the degree of hallux valgus deformity [58]. Intra- and inter-rater reliability have been found to be excellent, with kappa (κ) values of 0.77 and 0.86, respectively [57]. Foot deformity will be recorded if any of the following are present:Hallux abducto valgus (graded in accordance with the Manchester Scale) [35, 57];Hammer/claw toes [35];Bony prominences (e.g. prominent metatarsal heads);Charcot neuroarthropathy [35];Other (e.g. forefoot pad atrophy).

Limited joint range of motion (e.g. first metatarsophalangeal joint) has also been associated with an increased risk of foot ulceration in prospective and case–control studies [55, 56, 59].

Dorsiflexion range of motion of the first metatarsophalangeal joint will be assessed in accordance with the ‘static non-weightbearing technique 1’ described by Hopson et al. [60]. This technique has been shown to be a reliable clinical measurement (ICC = 0.95). Limited range of motion at the first metatarsophalangeal joint will be documented if:Passive, non-weightbearing dorsiflexion is <65° (either foot) [60].

Elevated peak plantar pressures have been found to be a statistically significant predictor of diabetic foot ulceration in prospective studies [61–63]. Peak plantar pressures will be assessed during level barefoot walking using a two-step gait initiation protocol [64] with the Tekscan Matscan® system (Tekscan Inc, South Boston, MA, USA). Peak plantar pressures will be measured at seven regions of the foot, including the heel, midfoot, first metatarsophalangeal joint, second metatarsophalangeal joint, third to fifth metatarsophalangeal joints, hallux, and lesser toes [64]. The mean peak plantar pressure values of the three trials (of each foot) will be used for the purposes of analysis.

